### Sample size

The sample size estimation is based on a two-sided alpha of 0.05, beta of 0.2 (power 0.8), ratio of intervention to control participants of 1:2, and efficacy of maintaining smoking cessation at 12 months of 3% in the control group and 13% in the intervention group. Based on these assumptions the sample size required will be 106 in the intervention group and 212 in the control group across both sites. Using a conservative estimate of 50% of the clients being smokers, we will be recruiting less than 20% of regular DAHS and OVAHS clients for the trial. To take into account those lost to follow up (e.g. deaths), the aimed sample size is 120 in the intervention group and 240 in the control group across both sites.

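### The stated requirement of 106 intervention and 212 control participants does not follow from its printed inputs; the standard continuity-corrected formula gives 93 and 186, so the error is conservative

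*Protocol article*

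**What the plan says.** The Sample size section of the protocol article prints every input. The error rates are given as "The sample size estimation is based on a two-sided alpha of 0.05, beta of 0.2 (power 0.8" (closing bracket omitted here), the allocation as a "ratio of intervention to control participants of 1:2", and the effect as "efficacy of maintaining smoking cessation at 12 months of 3% in the control group and 13% in the intervention group". It then concludes: "Based on these assumptions the sample size required will be 106 in the intervention group and 212 in the control group across both sites". To allow for loss to follow-up, "the aimed sample size is 120 in the intervention group and 240 in the control group across both sites". No formula, software routine, continuity correction or loss rate is given.

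The direction of the allocation is not in doubt. The randomisation section puts 24 control and 12 intervention participants in each block of 36, and the section on planned recruitment repeats the target of 120 intervention and 240 control. The smaller arm is therefore the one with the assumed 13% quit rate.

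**The concern.** The article states both the inputs and the result, so the calculation can be repeated, and the result does not come out. With unequal allocation it matters which arm carries which rate. The rate nearer 50% has the larger variance, and putting it in the smaller or the larger arm changes the answer. A program that asks for group 1, group 2 and a ratio makes it easy to enter these the wrong way round.

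At stake is whether the stated size and the stated power belong together. If they do not, a reader misjudges the power the trial has and how much loss to follow-up the target of 360 can absorb. The second point matters here because the article reports that participants found the original six- and 12-month questionnaires difficult to complete.

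**Working it through.** **Inputs** (Sample size section): z for two-sided 0.05 = 1.960; z for 80% power = 0.842; difference d = 0.13 − 0.03 = 0.10; ratio of larger to smaller arm k = 2.

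**Formula.** With p1 in the smaller arm (n), p2 in the larger arm (kn) and p̄ = (p1 + k·p2)/(1 + k):

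- uncorrected: n = [1.960·√((1 + 1/k)·p̄(1 − p̄)) + 0.842·√(p1(1 − p1) + p2(1 − p2)/k)]² / d²
- continuity-corrected: n' = (n/4)·[1 + √(1 + 2(1 + 1/k)/(n·d))]²

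**1. Reproducing the printed figure (rates swapped: 3% in n, 13% in 2n).** p̄ = (0.03 + 0.26)/3 = 0.0967. The two terms are 0.7093 and 0.2463, so n = 0.9557²/0.01 = 91.3. Corrected: n' = (91.3/4)·(1 + √1.3285)² = 105.8, which rounds up to **106/212**, the printed figure.

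**2. The design as stated (13% in n, 3% in 2n).** p̄ = (0.13 + 0.06)/3 = 0.0633. The two terms are 0.5847 and 0.3007, so n = 0.8854²/0.01 = 78.4, giving **79/158** uncorrected. Corrected: n' = (78.4/4)·(1 + √1.3827)² = 92.8, giving **93/186**.

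**3. Size of the discrepancy.** 106 + 212 = 318 against 93 + 186 = 279: 39 participants, or 14%. Against the uncorrected 79 + 158 = 237 it is 81 participants, or 34%.

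**4. Other routes, arms as stated** (smaller-arm size):

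| Method | n |
|---|---|
| Arcsine, 80% power | 78 |
| Fisher's exact test, 80% power | about 80-81 |
| Unpooled variance, 80% power | 101 |
| Unpooled variance with correction, 80% power | 115 |
| Unweighted mean rate with correction, 80% power | 105.1 → 106 |
| Pooled with correction, 85% power | 105.7 → 106 |

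Two routes other than the swap therefore reach 106. One contradicts the stated 80% power. The other uses p̄ = (0.13 + 0.03)/2, which is not the standard form for 1:2 allocation.

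**5. Power under the stated rates.** The corrected approximation is Φ[(d − ½(1/n1 + 1/n2) − 1.960·SE0)/SE1]. At 106/212, SE0 = 0.02897, SE1 = 0.03470 and the correction is 0.00708, so the argument is 1.041 and the power 85.1%. The exact columns sum the binomial probabilities of all tables that each test rejects.

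| Size | Corrected formula | Uncorrected formula | Exact: unpooled Wald | Exact: corrected chi-square | Exact: Fisher | Exact: chi-square |
|---|---|---|---|---|---|---|
| 93/186 | 80.1% | 85.6% | 81.4% | 83.1% | 85.5% | 88.0% |
| 106/212 | 85.1% | 89.3% | 87.0% | 87.7% | 89.8% | 91.7% |
| 120/240 | 89.2% | 92.4% | 91.2% | 91.2% | 93.1% | 94.5% |

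**6. Loss allowance.** The target of 120 against 106 implies 1 − 106/120 = 11.7% loss. Against 93 it is 1 − 93/120 = 22.5%.

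**The case against.** The strongest reply is that the article does not name its formula, so no single figure can be called the right one. With the arms as stated and 80% power, approximations run from 78 to 115 in the smaller arm, and 106 lies inside that range. The Treatment effects section plans simple rates with 95% confidence intervals first, which would be compatible with an unpooled variance. On the corrected unpooled formula, 106 would even be about 8% short.

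Part of this stands. The figure of 93/186 depends on the continuity correction and the pooled formula, and must be labelled so. But the unpooled formulas do not give 106 either, and their larger numbers are not borne out by exact calculation: an unpooled Wald test already has 81% power at 93/186 and 87% at 106/212. Under every test tried, 80% understates the power at 106/212.

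A reader might also draw three stronger conclusions, which the documents do not support.

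- **That the arms were certainly reversed.** The match is exact and this is the likeliest explanation, but with no formula shown it remains an inference, and two other routes reach the same number.
- **That wrong power means too little power.** The error runs the other way.
- **That the inflated figure led to the wider entry criterion or the contingency interim analysis.** The Protocol deviations section does mention meeting the sample size, but it gives as reasons that very few people met the readiness criterion and that a broader population was more appropriate. The interim analysis is tied to difficulty in recruiting 360 and to the investigators' discretion. Nothing shows that a requirement of 279 rather than 318 would have changed either.

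**Conclusion.** The point holds as a reporting error in the sample size paragraph. Under its own inputs, 106/212 is not the requirement for 80% power. By the standard pooled formula the requirement is 93/186 with continuity correction and 79/158 without, so the printed total is 39 participants (14%) above the like-for-like figure. The comparison is like for like because the pooled formula reaches 106 with the arms swapped only when the correction is applied.

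The error is conservative. If the 3% and 13% rates hold, 106/212 has about 85% power by the corrected formula and 87-92% by exact enumeration, and 120/240 has about 89% or more. The trial is not underpowered for the stated effect, and the practical consequence is a wider margin for loss to follow-up than the paragraph implies. The mismatch between inputs and result is certain for the standard formula; its cause is likely but unproven.

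**What to change.** In the Sample size section, name the formula and say whether a continuity correction was used. Then make the size and the power agree in one of two ways:

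- give 93 intervention and 186 control as the requirement for 80% power by the continuity-corrected formula, and note that 120/240 then allows about 22.5% loss; or
- keep 106/212 and state the power as about 85% by that formula, with the implied loss allowance of 11.7%.

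If another method was used, such as 85% power or a different variance, state it so that the figure can be reproduced. The cost is rewording one paragraph. The target of 360, the randomisation lists and the trial procedures need not change.

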### Recruitment strategies

Participants are being actively and opportunistically recruited. Active recruitment is facilitated by the Project Manager or Aboriginal researchers through incidental encounters in the community, family and community links. The participants do not need to see health care staff prior to being recruited, but are referred to the primary health care clinic afterwards.

Participants are being passively recruited through OVAHS and DAHS routine clinic visits as well as through running dedicated Adult Health Check clinics ('Aboriginal and Torres Strait Islander Adult Well Persons Check') for overdue clients - clients known or found to be current smokers are offered participation in the trial by clinic health workers: ***"Have you thought about cutting down or quitting? Do you want to know what we can offer?" ***(see Figure 1 for a flow diagram explaining the steps involved).

### Planned recruitment rate and risk of loss to follow up

We aim to recruit 12 people (approximately 8 control, 4 intervention) monthly for 15 months. This regular staggered recruitment is to ensure that a maximum of 38 participants will be followed up by the four half-time Aboriginal researchers in any one week period. This will allow for variations to the scheduled recruitment without placing too much pressure on resources. The trial should be completed in 26 months.

As it proved difficult for participants to complete the original six and 12 month questionnaires, an alternative, minimal data collection tool was created. If participants leave Derby or Kununurra the Aboriginal researchers attempt to administer the final questionnaire by alternate means (e.g. phone, Facebook) and arrange for a local health care clinic to collect urine samples.

If recruitment of 360 participants (120 intervention and 240 control) is proving difficult within the time frame of the trial, an interim analysis of primary endpoints will be performed. It should be noted that the requirement for an interim analysis will be at the discretion of the investigators and anticipated speed of recruitment. If required, an interim analysis is to be undertaken by the Data Safety and Monitoring Committee (DSMC) once 50% of the participants (60 in the intervention and 120 in the control group) have completed the study. If this demonstrates a difference that is deemed by the DSMC to be statistically and clinically significant then the DSMC will provide advice to the supervising Human Research Ethics Committees (HREC) regarding whether the trial should be terminated.

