### Blinding

Due to the nature of the intervention and the 2:1 weighting of participants in the control and intervention arms, the participants, research team and local healthcare staff know whether each participant belongs to the control or intervention group. The staff performing the urinary cotinine assay are unaware of the allocation.

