### Treatment effects

Analysis of the primary outcome will involve comparing the quit rate between the two groups. Simple unadjusted rates and 95% confidence intervals will be obtained in the first instance, with subsequent multiple regression analysis adjusting for other variables. Two forms of regression analysis will be considered for the primary outcome - logistic and Cox proportional hazard. Analysis of secondary outcomes will be conducted using standard statistical procedures applicable to categorical or continuous data. All tests of significance will be two-tailed.

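### The optional interim comparison of quit rates has no pre-set boundary and leaves the final test unadjusted; if 0.05 is used at both looks, the type I error can reach about 8%

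*Protocol article*

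**What the plan says.** The rule is in the protocol article under Planned recruitment rate and risk of loss to follow up. If recruiting 360 people proves difficult, the primary endpoint is analysed at an interim point.

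- **Who calls it:** "the requirement for an interim analysis will be at the discretion of the investigators and anticipated speed of recruitment".
- **When:** the Data Safety and Monitoring Committee (DSMC) does the analysis "once 50% of the participants (60 in the intervention and 120 in the control group) have completed the study".
- **Criterion:** "If this demonstrates a difference that is deemed by the DSMC to be statistically and clinically significant", the DSMC advises the supervising ethics committees on whether to terminate.

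The only significance level in the article is in the Sample size section, which assumes a "two-sided alpha of 0.05, beta of 0.2 (power 0.8"). The Treatment effects section adds "All tests of significance will be two-tailed". Neither section mentions an interim look.

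The Blinding section says that "the participants, research team and local healthcare staff know whether each participant belongs to the control or intervention group"; only the cotinine assay staff are unaware of allocation. The Data monitoring section describes the DSMC as an ad hoc committee, convened for adverse events or protocol deviations.

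**The concern.** An interim comparison that can end a trial for benefit gives a second chance of a false positive result. The overall error stays at the planned level only if the interim criterion is strict enough, or if the final test is adjusted. Here the criterion is a judgement made after the DSMC has seen the data, and the final test stands as if no look had occurred. The decision to look is also open, and it rests with investigators in a trial without blinding. At stake are the error rate of the primary comparison and the credibility of any early stop.

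The second part of the concern is fit. The look is a response to slow recruitment, but it needs 180 people to have passed a 12-month endpoint. It is therefore available late, and it may not help with the problem that triggers it.

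**Working it through.** **Inputs.** From Sample size: two-sided 0.05; quit rates of 3% (control) and 13% (intervention); target 240 and 120. From Planned recruitment rate: interim at 120 and 60 completers; 12 recruits a month for 15 months; trial complete in 26 months. From Outcome measures: a 12-month endpoint. The interim level is not stated, so 0.05 is an assumption and a range is shown.

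**The plan's own figures.** The article gives no interim error rate to reproduce. 60 + 120 = 180 is half of 360, so the information fraction is t = 0.5. Recruitment does not reconcile: 12 × 15 = 180, not 360. Reaching 360 in 15 months needs 360/15 = 24 a month, which is 12 a month only if that rate is per site. Both rates are used below. (The stated 106 and 212 were not reproduced either: the stated inputs give 79/158, or 93/186 with continuity correction. Nothing below uses them.)

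**Type I error, normal theory.** With Z1 at the interim and Z2 at the end, the correlation is √0.5 = 0.707, and the error is P(|Z1| > c1 or |Z2| > c2).

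| Interim p | Final p | Overall type I error |
|---|---|---|
| 0.05 | 0.05 | 8.31% |
| 0.03 | 0.05 | 6.8% |
| 0.01 | 0.05 | 5.5% |
| 0.001 | 0.05 | 5.02% |
| 0.00305 | 0.049 | 5.00% |

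**Type I error, binomial simulation.** One million trials per setting, unadjusted chi-square at 60/120 and then 120/240, 0.05 at both looks: 7.1% at a common quit rate of 3%, 8.0% at 6.3%, 8.5% at 10% and 8.5% at 13%.

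**Events at the look.** Under the design rates, 60 × 0.13 + 120 × 0.03 = 11.4 quitters are expected. As an illustration only, suppose the truth is 8% against 3% and the interim level is 0.05. Then 33% of trials cross at the interim, with a mean observed difference of 9.2 points against a true 5.

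**Timing.** With steady accrual of r a month and no loss, the look falls at month 180/r + 12, and recruitment of 360 ends at month 360/r.

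| r per month | Look | Recruitment of 360 ends |
|---|---|---|
| 24 | 7.5 + 12 = 19.5 | 15 |
| 20 | 9 + 12 = 21 | 18 |
| 15 | 12 + 12 = 24 | 24 |
| 12 | 15 + 12 = 27 | 30 |
| 10 | 18 + 12 = 30 | 36 |

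Setting 180/r + 12 < 360/r gives r < 15. At 24 a month the look comes 4.5 months after recruitment closes. At 12 a month it comes after the stated 26-month end, with 12 × 27 = 324 enrolled. (If each month's recruits all enrolled at its start, that look would fall at month 14 + 12 = 26, the stated end itself.) Loss to follow-up would make every look later.

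**Cost of a strict boundary.** At the design rates the pooled rate is 11.4/180 = 0.0633. At the interim, the standard error under no difference is √(0.0633 × 0.9367 × (1/60 + 1/120)) = 0.0385. Under the alternative it is √(0.13 × 0.87/60 + 0.03 × 0.97/120) = 0.0461. The chance of crossing is Φ((0.10 − z × 0.0385)/0.0461): about 70% at p<0.05 (z = 1.960), 38% at p<0.003 (z = 2.968) and 28% at p<0.001 (z = 3.291). At 120/240 both standard errors are divided by √2, and final power is 92.4% at 0.05 and 92.3% at 0.049.

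**The case against.** **The 8% depends on choices that the article does not make.** This stands. The figure needs 0.05 at the interim, a look that always takes place, significance alone stopping the trial, and an unadjusted chi-square. The article makes the look contingent, asks for clinical as well as statistical significance, and has the DSMC advise rather than decide. With Fisher's exact test at both looks, simulation gives 5.1% at a 3% common rate, 6.0% at 6.3% and 6.5% at 13%. If an interim stop also needs an observed difference of at least 10 points (an illustrative threshold), the error runs from about 4.6% at 3% to about 8% at 13%. A reader might infer that the trial's false-positive rate simply is 8%; the article does not support that.

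**The look could still shorten recruitment.** This also stands. The trigger is slow accrual, and below 15 a month the look comes before 360 are enrolled. A reader might infer that the look can never serve its purpose. That holds only if the 15-month recruitment and 26-month trial are kept, or if accrual lies between 15 and 24 a month.

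**The investigators do not run the analysis.** Correct. They decide only whether it happens; its timing is fixed and the DSMC performs it. They know individual allocations, but the article does not say that they see quit rates by arm. The endpoint also needs cotinine confirmation, assayed by staff unaware of allocation. A reader might infer that investigators could call the look because they had seen a favourable result; the article does not show this. What remains is that an optional look should not rest on discretion in an open-label trial.

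**A boundary may be in the full protocol, the analysis plan or a DSMC charter.** It may. But this section already fixes the timing, who calls the look, who performs it and the criterion, and that criterion is a judgement. A boundary set elsewhere would have to replace this wording, not sit beside it.

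**Conclusion.** The point holds in conditional form. As written, the optional look leaves the type I error uncontrolled, because the criterion is a judgement, the final test is unadjusted and the decision to look is discretionary. If the article's only stated level is used at both looks, the error can reach about 8% (8.3% by normal theory; 7.1% to 8.5% by simulation). This assumes that the look is always taken at half information and that significance alone stops the trial. Less frequent looks, an exact test or a genuine clinical threshold reduce it, in some settings to about 5%.

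The mismatch of trigger and timing is secondary. Within the stated time frame the look comes after recruitment closes or after the stated end, but in a slow, overrunning trial it could still save recruitment.

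**What to change.** - **For slow recruitment:** replace the comparative look with a review of accrual, loss to follow-up and the pooled quit rate, with no comparison by arm. This addresses the trigger and uses no type I error.
- **If the efficacy look is kept:** state in advance that it takes place at 180 completers whatever the investigators' view. Set a boundary: either p<0.001 with the final test at 0.05 (overall 5.02%), or O'Brien-Fleming-type limits of about 0.003 at the interim and 0.049 at the end (overall 5.0%). The DSMC's clinical judgement should apply only once that boundary is crossed.
- **In the same amendment:** reconcile the recruitment rate with the target of 360, so that the timing of the look can be stated.

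The cost is a short amendment and a lower chance of stopping early: at the design rates, about 28% (p<0.001) or 38% (p<0.003) instead of about 70% at p<0.05. Final power is almost unchanged: no change with the final test at 0.05, and about 0.1 percentage point lower at 0.049.

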### Withdrawal criteria

Participants may be withdrawn from the study if one or more of the following occurs:

• Voluntary withdrawal: a participant can voluntarily withdraw at any time without having to provide a reason for doing so

• Death

• Significant illness requiring prolonged hospitalisation

• A serious and irreconcilable protocol violation (as determined by the investigators)

### Data management

All information is initially recorded by Aboriginal researchers on paper forms. Paper records are stored under numerical code in a locked filing cabinet only accessible to study personnel. All information collected from participants are treated as strictly confidential. Administrative staff will then transpose this information to a password-protected Access 2007 database (Microsoft, Redmond, WA, USA). De-identified data will be stored in password protected computers.

### Data monitoring

The DSMC is an ad hoc committee to be convened in the event of an expected adverse event, serious adverse event or protocol deviation. Any change or alteration from the procedures stated in the study protocol, consent document, recruitment process, or study materials (e.g. questionnaires) originally approved by the HREC are considered to be protocol deviations. Notification to the DSMC and reporting of the DSMC to the supervising HREC will occur if there is 1) any unexpected medical event in a participant involved in the trial as per the streamlined reporting scheme recommended by the National Health and Medical Research Council (NHMRC) and Australian Health Ethics Committee [28] or 2) a protocol deviation.

All recorded information will be assessed at least monthly by the Project Manager. The data stored on the relational database described above will be randomly assessed to make sure there are no errors in transcribing.

### Data analyses

Data from the trial will be entered into the database described above and then extracted into Stata, version 12 (StataCorp, College Station, Tex, USA). Analysis of questionnaire data will be descriptive and utilise univariate parametric and non-parametric analysis to identify differences between the control and intervention group and the intervention group prior to and following the intervention.

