### Inclusion criteria

Participation in the trial is based on the following inclusion criteria:

• Aboriginal and/or Torres Strait Islander

• ≥ 16 years of age

• Self-reported current smoker or quit within 2 weeks of recruitment

• Thinking about cutting down or quitting smoking

• A regular client of Derby Aboriginal Health Service (DAHS) in Derby or Ord Valley Aboriginal Health Service (OVAHS) in Kununurra

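### The questionnaire analysis includes an uncontrolled before/after comparison in the intervention arm alone, which can be significant with no program effect; the randomised primary analysis is not affected

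*Protocol article*

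**What the plan says.** The Data analyses section of the protocol article states: "Analysis of questionnaire data will be descriptive and utilise univariate parametric and non-parametric analysis". The purpose given is to "identify differences between the control and intervention group and the intervention group prior to and following the intervention". Two contrasts are therefore named: the randomised one, and the intervention arm against its own baseline. No before/after comparison is named for the control arm.

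The primary outcome is handled separately under Treatment effects: "Analysis of the primary outcome will involve comparing the quit rate between the two groups". That section adds confidence intervals and regression, and makes all significance tests two-tailed. The Baseline characteristics section plans unadjusted and adjusted comparisons of the two arms.

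The Inclusion criteria define who enters: "Self-reported current smoker or quit within 2 weeks of recruitment", and "Thinking about cutting down or quitting smoking". The Sample size section assumes "efficacy of maintaining smoking cessation at 12 months of 3% in the control group and 13% in the intervention group". One secondary endpoint under Outcome measures is the proportion of participants reporting a cut of at least 20% in weekly cigarettes.

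**The concern.** A before/after contrast in one arm measures the program plus everything else that changes over the same months. Four features of this trial make that background change likely, or make it look like benefit:

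- Eligibility requires people to be considering smoking less, so some would do so unaided.
- Controls receive cessation advice and pharmacotherapy as usual care, and the plan itself expects 3% of them to quit.
- The endpoint of at least a 20% cut is zero at entry by definition, so it can only rise.
- Outcomes are self-reported by participants who know their allocation, and the researchers who deliver the program also administer the questionnaires. Without a concurrent group, drift in reporting cannot be seen.

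The outcomes exposed are those drawn from the questionnaire: consumption, self-rated health and self-reported quitting at 6 months. If the arms did not differ on these, a prespecified and significant before/after result would still be available to report as apparent benefit.

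**Working it through.** The plan gives no figure for the within-arm contrast, so there is none to reproduce. The check asks how often a within-arm test would be significant at two-sided 5% if the program did nothing.

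**Inputs from the protocol article (Sample size).** Control quit rate 3%; intervention arm 106 (required) or 120 (target); control arm 212 or 240; two-sided alpha 0.05.

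**Assumptions, not in the document.** Everyone enters smoking (relaxed in step 4). For consumption, a drift of 0.1 to 0.3 SD in the absence of any program effect, and a baseline/follow-up correlation r of 0.4 to 0.8. The article names no specific test; McNemar and the paired t-test stand in for its non-parametric and parametric analyses.

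**Step 1: cessation within the intervention arm.** If all enter smoking, every change is in one direction. With k quitters the exact McNemar p-value is 2 × 0.5^k. For k=5 this is 0.0625; for k=6 it is 0.031. At least 6 quitters are needed. The uncorrected asymptotic McNemar statistic equals k, so k=4 exceeds the critical value of 3.84.

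With no program effect, the number of quitters is binomial(n, 0.03), with a mean of 106 × 0.03 = 3.2 or 120 × 0.03 = 3.6.

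| n | exact, P(at least 6) | asymptotic, P(at least 4) |
|---|---|---|
| 106 | 0.10 | 0.39 |
| 120 | 0.15 | 0.49 |

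**Step 2: the randomised contrast under the same conditions.** With 3% in both arms, the error rate by enumeration is 0.044 (pooled z) or 0.033 (Fisher) for 212 v 106, and 0.046 or 0.034 for 240 v 120. It stays below 5%.

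**Step 3: sensitivity to the background quit rate.** For the exact within-arm test at n=120, the probability of significance is 0.56 at 5%, 0.92 at 8% and 0.98 at 10%. The article gives no usual-care rate this high. The 5-22% in its Background comes from participants in trials who were not interested in quitting at the start.

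**Step 4: recent quitters at entry.** Someone who has just quit can only stay quit or relapse, which pushes the cessation contrast towards worsening. A simulation at n=120 with 3% new quits and an assumed 85% relapse gave:

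| recent quitters at entry | significant improvement | significant worsening |
|---|---|---|
| 0% | 15% | 0% |
| 5% | 0.2% | 4% |
| 10% | under 0.1% | 39% |

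The direction of the bias therefore depends on the entry mix.

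**Step 5: cigarettes per week.** For a paired t-test at n=106 with standardised drift d, the standard error is sqrt(2(1−r)/n). For r=0.4 this is sqrt(1.2/106) = 0.106, so d=0.2 gives a noncentrality of 0.2/0.106 = 1.88 and a probability of significance of 0.46. The full grid is:

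| drift (SD) | r=0.4 | r=0.6 | r=0.8 |
|---|---|---|---|
| 0.1 | 0.15 | 0.21 | 0.36 |
| 0.2 | 0.46 | 0.63 | 0.90 |
| 0.3 | 0.80 | 0.93 | 0.998 |

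Only n comes from the document here. The table shows sensitivity and does not predict this trial.

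**The case against.** The strongest reply is that the before/after look adds to the randomised analysis and replaces nothing. The same sentence lists the between-arm comparison first, Treatment effects governs the primary outcome, and the missing-data section sets intention to treat. The work is called descriptive, no p-value is mentioned, and nowhere does the article say that a before/after result will count as evidence of efficacy. All of this stands, except that the descriptive label does not settle the matter: the sentence names parametric and non-parametric analysis as the means of finding differences, and puts the uncontrolled contrast on the same footing as the randomised one.

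A reader might infer that the trial gives up its randomised comparison. The documents show the opposite. A reader might also infer that the intervention arm is bound to show a change. At the plan's own 3% rate an exact test would be significant in only 10-15% of trials, and even the uncorrected asymptotic test stays below half. Near-certainty needs background rates of about 8-10%, or the larger assumed drifts in consumption, and the article supports neither. Counting just-quit entrants as a reason for apparent improvement is also wrong; they work against it. Nor do the entry criteria select on high consumption, so regression to the mean is not an established mechanism here.

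It can also be said that baseline adjustment for every outcome asks too much. That is fair for cessation, where baseline status is nearly constant by eligibility, and the fix is limited accordingly.

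**Conclusion.** The point holds as a free improvement. The article commits to an uncontrolled contrast in one arm, and a significant result from it could not be attributed to the program. On the document's 3% rate, and assuming all enter smoking, its false-positive rate is about 10% (n=106) to 15% (n=120) with an exact test, and 39% to 49% with an uncorrected asymptotic one, against 3% to 5% for the randomised comparison. For consumption the range is about 15% to 99.8%, resting wholly on the assumed drift and correlation. Recent quitters at entry can reverse the direction for cessation, so that contrast is hard to read either way. The cotinine-confirmed primary comparison and the conclusion drawn from it are not at risk.

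**What to change.** In Data analyses, remove the before/after tests within the intervention arm. State that all inference on questionnaire outcomes rests on the between-arm difference at 6 and 12 months, with the baseline value as a covariate for outcomes that vary at baseline, such as cigarettes per week and self-rated health. If change from baseline is shown, show it for both arms as description, without p-values.

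The cost is about one sentence of text. Questionnaires at baseline, 6 and 12 months are already planned for both arms, so no new data or participants are needed.
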